### Missing data

We anticipate missing data, but estimate that no more than 10% of women will have missing usable data on primary outcome, eligibility, setting of cervical ripening and/or have some part of the baseline data (age, comorbidities and any relevant identified hospital-level factors). We will use evidence-based strategies to minimise any such losses and recover any missing data that is possible. We will monitor levels of missing data as the study progresses, identifying any outcomes or exposures and/or sites that are prone to missingness, and take corrective action (eg, additional feedback and support). We will conduct appropriate sensitivity type analyses, for example, using a multiple imputation approach assuming data are missing at random, and if the data warrant (eg, if there is differential missingness between the in-hospital and at-home cohorts) non-ignorable (informative) missing data generating mechanisms.

We will also conduct an exploratory analysis comparing the two methods of home IOL, that is, dinoprostone versus mechanical methods. We will use the same methods as outlined above for the primary and secondary outcomes in the overall analysis.

#### Sample size

The sample size is based on our principal analysis (women with singleton pregnancies having IOL at 39 weeks’ gestation or more) and primary comparison (home cervical ripening vs in-hospital cervical ripening with dinoprostone), estimated 6% NNU admission rate^1^ for babies born to mothers having IOL at >39 weeks’ gestation with no more than 4% excess NNU admission rate (from 6%), at 90% power, 2.5% one-sided alpha and an estimated ICC of 0.01. We will require 160 women in each of 12 sites (clusters) with uncomplicated pregnancies at 39 weeks or more undergoing IOL (total 1920 in each arm). To account for the fact that (a) only around 50% of women eligible for home cervical ripening in the intervention arm will actually initiate home cervical ripening, and (b) a larger pool of women is required in the control arm to allow for propensity score matching, our required sample size is 1920×2 (number of arms)/0.5 (numbers of women actually starting home cervical ripening and matching)/0.9 (for missing data), giving an overall required sample size of 8533.

Based on an estimate that 22% of all maternities have IOL at 39 weeks or more^1^ and that ~29% of these would be eligible for participation in our principal analysis (from scoping data from potential participating sites), and, in home cervical ripening sites ~50% of these will take up home cervical ripening, we anticipate achieving our recruitment targets within 20 months.

Current data from the National Maternity and Perinatal Audit (NMPA) for 2019 suggests that the national average rate of IOL after 37 weeks is 29.6%.^1^ As our proposed participating units have about 90 000 births per annum, we anticipate collecting data on approximately 41 000 women having IOL at 37 weeks’ gestation or more.

#### Participant identification and opt out

Participants will be identified from data recorded in specified fields in electronic maternity records. We will use data fields indicating IOL, estimated due date and date of IOL to identify women having IOL at 37 weeks’ gestation or more.

Women will be made aware of the CHOICE study through posters in participating sites; business cards; information leaflets; online adverts on hospital/maternity websites and relevant social media sites; and information in maternal electronic maternity records.

Women will be able to opt out of data provision by notifying their clinician or midwife, or emailing the study research midwife at the local site, and it will be recorded on their electronic record. There will be no restriction on co-enrolment in other studies.

#### Pilot phase

We propose a pilot phase to determine the parameters of the primary outcome and feasibility of obtaining the required sample size for analysis. This is based on the evaluable comparison group of 1920 women in each arm, so acts as an inherent check on home cervical ripening eligibility and uptake rates, the assumed level of missingness and attrition due to non-matching. We will assess variation of the primary outcome at the pilot stage, along with that of other measures of neonatal morbidity included as secondary outcomes (eg, any NNU admission and neonatal intensive care unit admission). We may redefine the parameters of NNU admission used in the primary outcome after analysis of pilot data, choosing the one with the lowest ICC or the one representing the least severe outcome, which has an ICC of 0.01 or less. This decision will be made in consultation between the expert project management group, the trial steering committee and the funder.

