## Methods and analysis

### CHOICE: a prospective cohort study

#### Study design and setting

We will carry out a prospective multicentre cohort study using de-identified clinical data from electronic hospital records. The primary outcome will be non-inferiority of a neonatal unit (NNU)/special care admission for 48 hours or longer, initiated within 48 hours of birth.

The study will be performed in at least 26 UK obstetric units, 14 of which offer exclusively in-hospital cervical ripening and 12 offer dinoprostone cervical ripening both in-hospital and at home.

Participating maternity units will be purposively selected to represent the diverse range of maternity service settings in the UK, and include urban tertiary referral units, mid-sized urban district general hospitals and small, more isolated, rural units.

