#### Exposure and outcomes

Our primary aim is to compare home versus in-hospital cervical ripening. We will collect data at individual level. The exposure group will be women who, at the start of the cervical ripening process, plan to have home cervical ripening. The comparator group will be women who planned to have in-hospital cervical ripening from maternity units not offering home cervical ripening. This will minimise potential bias arising from the fact that, in maternity units which offer both home and in-hospital cervical ripening, the risk of complications in the babies of women having home cervical ripening (lower risk pregnancies) is inherently different to that of babies of women having in-hospital cervical ripening (higher risk pregnancies).

As the NICE recommended agent for cervical ripening is vaginal prostaglandin, our primary comparison will be home dinoprostone versus in-hospital dinoprostone. Dinoprostone is now most commonly administered as 10-mg slow-release pessary (Propess, Ferring), which stays in place for 24 hours. We will use this formulation in our primary comparison.

We will include a secondary exploratory comparison—home cervical ripening with balloon catheter (exposure) versus home cervical ripening with dinoprostone (comparator), to explore if there are any indications of different safety profiles of these two methods of home cervical ripening.

Our proposed primary outcome will be admission to an NNU/special care baby unit for 48 hours or longer, initiated within 48 hours of birth. NNU admission is a marker of neonatal morbidity and is the leading core outcome defined for studies of IOL.^14^ Any increase in NNU admission of term babies is undesirable due to the separation of mother and baby. However, NNU admission rates are highly variable between maternity units and are likely to depend on local policies and culture. We, therefore, plan to use a primary outcome, which represents more severe neonatal morbidity (admission to a NNU within 48 hours of birth for 48 hours or longer), which is less likely to be influenced by site-specific factors. We may re-define the parameters of NNU admission used in the primary outcome after analysis of pilot data (see section ‘Pilot phase’).

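### The pilot rule for redefining the primary outcome has two unordered criteria that can select different endpoints after outcome data are seen, and the planning rate and margin are not tied to the choice

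*Protocol article*

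**What the plan says.** The current primary outcome is neonatal unit (NNU) admission lasting at least 48 hours and starting within 48 hours of birth. Under Exposure and outcomes the article adds: "We may re-define the parameters of NNU admission used in the primary outcome after analysis of pilot data". The Pilot phase section repeats this and gives the criterion: "choosing the one with the lowest ICC or the one representing the least severe outcome, which has an ICC of 0.01 or less". Other neonatal measures will be examined alongside the current outcome ("eg, any NNU admission and neonatal intensive care unit admission"). On who decides: "This decision will be made in consultation between the expert project management group, the trial steering committee and the funder".

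Three other statements bear on the point.
- The primary comparison is between sites: "The comparator group will be women who planned to have in-hospital cervical ripening from maternity units not offering home cervical ripening".
- The site mix is "14 of which offer exclusively in-hospital cervical ripening and 12 offer dinoprostone cervical ripening both in-hospital and at home".
- The Sample size section uses an "estimated 6% NNU admission rate", an absolute margin of 4 percentage points and an ICC of 0.01.

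**The concern.** The two criteria are joined by 'or', and nothing says which takes precedence. One minimises the ICC. The other accepts any ICC up to 0.01 and then prefers the mildest outcome. Where they disagree, the deciding bodies may follow either, and they do so after pilot outcome data have been analysed. The article does not say that they will lack results by home or in-hospital group.

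Three further questions follow. Does the lowest ICC identify the outcome least affected by site practice, or simply the rarest one? Could the ICC carry the home v in-hospital difference, given that the comparison is between sites? Do the planning rate and margin still make sense if the outcome changes? At stake is whether the endpoint of the non-inferiority claim can be shown to have been fixed independently of the results.

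**Working it through.** **1. The plan's own figure.** Inputs from Sample size: rate 6%, margin 0.04, one-sided alpha 0.025, power 90%, ICC 0.01, 160 women in each of 12 sites.
- Individual n per arm = (1.960 + 1.282)² × 2 × 0.06 × 0.94 / 0.04² = 741.
- Design effect = 1 + (160 − 1) × 0.01 = 2.59.
- 741 × 2.59 = 1919, i.e. 12 × 160 = 1920 per arm.

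The stated figure reproduces. The 0.01 in the pilot rule is therefore the value that supports the sample size, and there it is a per-arm quantity.

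**2. ICC and event rate.** For a fixed site variance s² on the logit scale, ICC ≈ s² × p(1 − p). Setting ICC = 0.01 at p = 0.06 gives s² = 0.01/0.0564 = 0.177. Then:
- p = 3%: 0.177 × 0.0291 = 0.005
- p = 1%: 0.177 × 0.0099 = 0.002

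Numerical integration of a logit-normal site effect gives 0.0018 at 1%, 0.0036 at 2%, 0.0053 at 3%, 0.010 at 6% and 0.0156 at 10%.

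**3. Can the two criteria disagree?** Take three nested definitions with assumed rates of 2%, 6% and 10% and equal logit-scale site variation. Their ICCs are 0.0036, 0.010 and 0.0156. The lowest-ICC criterion selects the 2% definition. The mildest definition with ICC of 0.01 or less is the 6% one. The same data lead to two different primary endpoints, both consistent with the text.

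**4. If the ICC were pooled over site types without exposure.** With w = 12/26 of sites offering home ripening and a difference d between groups, the amount added to the ICC is w(1 − w)d² / [p̄(1 − p̄)], where w(1 − w) = 0.2485.
- 6% v 10%: 0.2485 × 0.0016 / (0.0785 × 0.9215) = 0.0055
- 6% v 8%: 0.2485 × 0.0004 / (0.0692 × 0.9308) = 0.0015
- 6% v 2%: 0.2485 × 0.0016 / (0.0415 × 0.9585) = 0.010

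The 6% v 8% line also covers a 4-point excess among home women when all eligible women at home sites enter the ICC, at the protocol's 50% uptake (0.5 × 4 = 2 points, taking 6% in the others).

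The chance that the estimated ICC is 0.01 or less was simulated with 14 + 12 equal-sized sites, a true within-group ICC of 0.005 (assumed) and 20,000 runs:

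| Women per site (assumed) | Estimator | No difference | 6% v 10% | 6% v 2% |
|---|---|---|---|---|
| 160 | pooled | 0.93 | 0.48 | 0.15 |
| 160 | within site type | 0.92 | 0.92 | 0.90 |
| 20 | pooled | 0.68 | 0.54 | 0.46 |

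**5. Rate and margin.** At 6%, a 4-point margin allows 10%, a ratio of 1.67. At an assumed 2% it would allow 6%, a ratio of 3.

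**The case against.** The redefinition is announced in advance, confined to the parameters of NNU admission, and decided with the steering committee and the funder. A sequential reading, with the mildest definition that meets 0.01 and otherwise the lowest ICC, would remove the conflict. The raw-scale ICC is what enters the design effect, so it is a legitimate feasibility criterion. The second criterion favours milder, usually commoner, outcomes and so pulls against rarity. The lowest ICC need not select the rarest definition if site variation differs between definitions, and the article argues that severe admissions are less subject to local policy. Estimator details may be in the analysis plan.

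Most of this stands, and it limits the point. It does not supply an order: the text does not state the sequential reading and puts the lowest ICC first. Announcing a choice in advance does not fix how it will be made.

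A reader might go further and infer that the rule tends to discard definitions on which home ripening looks harmful. The article does not support that.
- It does not say that the ICC is pooled over site types; the sample size uses a per-arm ICC, and an ICC estimated within site type shows no such dependence.
- Even a pooled ICC rises with the square of the difference, so it penalises benefit too, and more heavily in the example above.
- Under pooling, a definition with within-group ICC 0.005 and a 4-point excess still meets the threshold about half the time.
- The home sites also provide in-hospital ripening, so the added amount shrinks if all their eligible women are counted.

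**Conclusion.** The point holds as an ambiguity in a rule that the article itself fixes. Two unordered criteria, applied after pilot outcome data are analysed, can give different primary endpoints. This needs no assumption about how the ICC is computed.

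The tendency of the lowest-ICC criterion to favour rare definitions (0.010 at 6%, about 0.005 at 3%, 0.002 at 1%) rests on equal logit-scale site variation across definitions. Dependence on the group difference (about 0.0055 for 6% v 10%, about 0.0015 for a 2-point difference) is conditional on pooling without exposure, which is not stated; it would act in either direction. Pilot size and within-group ICC are assumptions throughout.

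The 6% rate and 4-point margin were set for the current outcome, and the article does not say that they follow a new one. The threefold ratio applies at an assumed 2% base rate.

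**What to change.** Before the pilot analysis:
1. State one ordered rule, for example the least severe definition with an ICC of 0.01 or less, and the lowest ICC only if none qualifies.
2. State that the ICC is estimated within exposure group, or in the in-hospital-only sites alone.
3. Make the choice without outcome results by home v in-hospital group.
4. Re-set the planning rate and margin for any new definition before the groups are compared.

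The cost is a few sentences and some precision in the ICC. With SE = (1 − r)(1 + (m − 1)r)√{2/[m(m − 1)(k − 1)]}, r = 0.01 and k = 26 sites, the SE is 0.0084 at an assumed 50 women per site and 0.0045 at 160. Estimating within exposure group over all 26 sites uses 24 rather than 25 degrees of freedom, which raises the SE by a factor of √(25/24) = 1.02. Using the 14 in-hospital-only sites alone raises it by √(25/13) = 1.39, to about 0.012 and 0.006. On either option the estimate is imprecise relative to a 0.01 threshold, which is a further reason to fix the order in advance.

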### CHOICE health economic analyses

Health economic analysis will be specified in a health economic analysis plan and reported in line with Consolidated Health Economic Evaluation Reporting Standards guidelines.^18^

Economic analyses will explore the cost effectiveness of at home versus inpatient cervical ripening for women undergoing IOL. Two separate cost-effectiveness questions will be addressed: (a) home cervical ripening with dinoprostone compared with in-hospital cervical ripening with dinoprostone and (b) home cervical ripening with balloon catheter compared with home cervical ripening with dinoprostone. The evaluation will involve within study cost-effectiveness analysis and a lifetime cost–utility analysis to account for any long-term impacts (cost and morbidity) of the alternative cervical ripening strategies. Resource use data will be obtained from the prospective multicentre observational cohort study using data obtained from the maternity information system, Badgernet Maternity and National Neonatal Research Database (NNRD) data.

Costs incurred by women and their families relating to IOL are relevant from the patient perspective and potentially important for the ‘at-home’ cervical ripening strategy. These data are not available from the observational datasets, and, therefore, tailored economic-related questions have been incorporated into a process evaluation survey described in section five below.

To account for bias in the observational data, methods such as multivariate regression and propensity scoring will be employed as recommended in guidelines for cost-effectiveness analysis based on observational data,^19 20^ which is consistent with the main study statistical analyses for this study. To capture any cost and morbidity events incurred in the neonatal period, the within-study analysis will include the primary study endpoint (NNU admission within 48 hours of birth for 48 hours or more) up to 1-month after birth. Outcomes will be reported as the incremental cost per NNU admission avoided (in line with primary study outcome) as well as incremental cost per birth up to 28 days after birth.

The lifetime analysis will account for longer term costs, quality of life, morbidity and disability from both the NHS and PSS and patient perspective and will report outcomes in terms of incremental cost per quality adjusted life years gained.

### Qualitative (q)CHOICE process evaluation

The process evaluation, nested within the observational cohort study, will comprise of a questionnaire-based survey in at least 12 sites and 5 case studies. Both qualitative and quantitative data will be collected, specifically a women’s experience questionnaire, semi-structured interviews with women and birth partners, audio recordings of clinician/women consultations, interviews and focus-group discussions with professionals. Figure 1 describes the initial process evaluation logic model hypothesising the chain linking interventions and outcomes. This will inform data collection and analysis. At the final stage of data analysis, we will share and discuss emerging findings with a group of service users to develop a revised logic model and explanatory framework.

**Figure 1 F1:**
[figure not shown]
Logic model for the qCHOICE process evaluation. ARM, artificial rupture of membranes; CR, cervical ripening; IOL, induction of labour; NHS, National Health Service; OPIOL, Home cervical ripening; qCHOICE, qualitative cervical ripening at home or in-hospital—prospective cohort study and process evaluation.

#### Questionnaire-based survey

Questionnaire data collection will take place over a 4–6-month period early in the study. CHOICE participating sites who use electronic maternity records accessible by women (the electronic equivalent of maternity hand-held records) will be invited to contribute to this part of the study. Women who have IOL at 39 weeks or more will receive a ‘push or SMS notification’ directing them to online study information when IOL is booked and a second notification around 10 days after they give birth. This will provide a link to the participant information sheets, consent form and online survey.

Push notifications are used by maternity services to prompt women to read information relating to their maternity care, including information within their electronic record. Women are able to opt out of SMS and push notifications, but routine monitoring of women’s use of their online record shows that a sufficient number of women use notifications and continue to access their record postnatally, thus enabling a broad sample to be reached.

The survey landing page will include a summary of qCHOICE and links to the information sheets before directing women to the consent questions, which they are asked to complete before completing the survey. A telephone number will be supplied for women to call if they have any questions about the survey, or to request a postal survey if preferred. Surveys will be submitted online via online surveys,^21^ by post or completed by phone with a member of the study team, with the support of an interpreter if needed. Participant contact details provided by survey respondents who are happy to be contacted further about a possible interview will be on a detachable back sheet of the questionnaire or a separate online page. Respondents will be informed that a £10 voucher will be offered to interview participants and that (with their consent) their birth partners may take part in an interview.

The survey will comprise validated tools as well as questions relating to service user costs, and the process of IOL as follows:

The Labour Agentry Scale (LAS; short form)^22^: the LAS is a well-established, validated measure of women’s experience during labour and birth. The short-form LAS includes 10 items with a 7-point Likert-type response. It measures perceived control during labour, which is the woman’s sense of mastery over internal and environmental factors and is highly correlated with satisfaction with care. The LAS will be the primary outcome.A modified version of the IOL satisfaction questionnaire^23^ tested in the Balloon Catheter Versus Propess for Labour Induction (PROBIT-F) trial.^24^ This questionnaire focuses specifically on women’s experiences of aspects of IOL, including information, anxiety and physical and emotional discomfort.The short-form Warwick-Edinburgh Mental Well-Being Scale (WEMWBS)^25^: a seven-item scale that measures mental well-being (as opposed to mental illness or disorder) representing positive attributes of well-being, including feeling and functioning.Additional questions, which will inform the economic analysis from the woman’s perspective, will cover resource use and expenditures of cervical ripening for women, including number of returns and phone calls to hospital, time distance, mode of travel to and from hospital, partner role, additional expenditure on maternity items and medication while at home, and additional childcare expenditure (if any) while at home.The survey will include demographic questions, questions about the process of IOL, questions relating to the impact of COVID-19 19 on their experience of IOL, a question asking women if they would be willing to be contacted regarding possible participation in a semi-structured interview and for permission for data linkage to the observational cohort study.

Survey data will be analysed using descriptive and inferential statistics. Descriptive statistics with 95% CIs will be reported for the total sample (by planned mode of cervical ripening—home or hospital, by actual mode (as some women who plan one mode may in practice have a different mode) and by study site). We will examine whether there are statistically significant differences in the primary outcome of sense of control (labour agentry) and by psychosocial outcome of postnatal psychological well-being score (WEMWBS) between women with home cervical ripening and women with in-hospital ripening. The covariates will include the reason for IOL, gestational age, maternal age, parity, sociodemographic status and ethnic group.

The sample size required to compare the experiences of women who had home and hospital cervical ripening is estimated to be 46 subjects within each of 12 sites (assuming equal numbers within each site), that is, 552 women in total. This is based on use of LAS^26^ where a change of 5.5 points is considered clinically meaningful. In an individually randomised study, to have 90% power at a 5% level of significance to detect an effect size of 0.5 (two-sided), we would need 85 evaluable subjects per arm (170 total). However, this has to be inflated for the clustering within each site. We assume that the intraclass correlation coefficient is 0.05 in this setting. We will also inflate the target sample by 10% to account for incomplete data/unusable questionnaires, aiming for 613 women in total.

We will invite all sites using accessible electronic maternity records to participate in the survey, but with the option to opt out. We will include at least 12 sites, that is, a total of at least 43 200 births annually across the sites. Our previous experience of questionnaire-based surveys, and the UK’s national maternity experience suggest a response rate of 40%. With an estimated eligibility of 22% of all maternities having IOL at 39 weeks or more, and 15% of these having home cervical ripening. We expect to achieve our sample size within 4 months and will monitor recruitment rates from each site and, if necessary, extend the survey period to ensure an adequate sample.

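### The survey's 552/613 target and 4-month duration assume equal arms, but the same section expects only 15% of eligible women to have home ripening

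*Protocol article*

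**What the plan says.** All of this is in the Protocol article under Questionnaire-based survey.

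- **Effect and power.** On the Labour Agentry Scale "a change of 5.5 points is considered clinically meaningful". The calculation is "to have 90% power at a 5% level of significance to detect an effect size of 0.5 (two-sided"), and without clustering "we would need 85 evaluable subjects per arm (170 total").
- **Clustering.** "We assume that the intraclass correlation coefficient is 0.05 in this setting". The required sample "is estimated to be 46 subjects within each of 12 sites (assuming equal numbers within each site), that is, 552 women in total". A 10% allowance for unusable questionnaires brings the aim to 613.
- **Accrual.** At least 12 sites with at least 43,200 births a year, 22% of maternities eligible, a 40% response rate, and "15% of these having home cervical ripening".
- **Duration.** "Questionnaire data collection will take place over a 4–6-month period early in the study", and later: "We expect to achieve our sample size within 4 months and will monitor recruitment rates from each site". The period may be extended if the sample is not adequate.

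The comparison to be powered is home against in-hospital ripening on the agentry score. The listed covariates do not include site. No quota, oversampling or target per arm is described.

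**The concern.** The sample size and the accrual forecast stand in consecutive paragraphs and use different allocations. The first is 1:1, which makes 552 evaluable women 276 home and 276 hospital. The second expects about 15:85. For a fixed total, an unequal split carries less information about the difference between arms, so a total that suffices at 1:1 need not suffice at 15:85.

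The total also ceases to be a useful progress marker. Hospital respondents would fill 613 quickly while home women remain the limiting group. The extension rule refers only to an adequate sample and the monitoring only to recruitment by site, so neither is tied to a home-arm number. At stake is the precision of the survey's primary comparison.

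**Working it through.** **1. The plan's own figures reproduce.** Effect size 0.5, 90% power and two-sided 5% give 85 per arm. Design effect (DE) = 1 + (46 − 1) × 0.05 = 3.25. Then 170 × 3.25 = 552.5, which matches 46 × 12 = 552, and 552/0.9 = 613. At 276 v 276 with DE 3.25, power is 90%.

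**2. Accrual on the stated minimum figures.**
- Four months: 43,200 × 4/12 = 14,400 births; × 0.22 = 3,168 eligible; × 0.40 = 1,267 respondents.
- Home: 1,267 × 0.15 = 190 (× 0.9 = 171 usable). Hospital: 1,077 (969 usable).
- A 1:1 split needs 276 usable home women, or 276/0.9 = 307 returns. At 190/4 = 47.5 a month this takes about 6.5 months. Six months gives 285 returns (257 usable).
- A total of 613 at 1,267/4 = 317 a month takes 1.9 months and includes 613 × 0.15 = 92 home women (83 usable).

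Four months is therefore too long for a total of 613 and too short for 307 home returns.

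**3. Power by the plan's method.** Power = Φ(0.5/√[DE × (1/h + 1/c)] − 1.96), where h and c are usable home and hospital women.

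| Sample | DE | Power |
|---|---|---|
| 276 v 276 | 3.25 | 90% |
| 83 v 469 (613 returned) | 3.25 | 64% |
| 171 v 969 (4 months) | 3.25, unchanged | 92% |
| 171 v 969 (4 months) | 5.70, at 95 per site | 71% |

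The 92% arises because 171 v 969 carries the information of 2 × 171 × 969/1,140 = 291 per arm, more than 276. The 71% arises because 1,140/12 = 95 women per site raises the design effect to 1 + 94 × 0.05 = 5.70.

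**4. Power by site mix.** This uses a random-intercept model with ICC 0.05 and total variance 1. The site splits are assumptions, because the article gives none for the survey.
- *Both arms in all 12 sites, site modelled, 83 v 469:* SE = √[0.95 × (1/83 + 1/469)] = 0.116, power 99%. With home women in only 6 or 4 of the 12 sites, power is 98% or 96%. For the 4-month intake it exceeds 99%.
- *Both arms in all 12 sites, arm-specific design effects, no credit for within-site covariance, 83 v 469:* about 6.9 home and 39.1 hospital women per site give design effects of 1.30 and 2.90, power 92%.
- *Separate sites, 6 home and 6 hospital, 83 v 469:* SE² = (0.05 + 0.95/13.8)/6 + (0.05 + 0.95/78.2)/6 = 0.0302, SE 0.174, power 82%. Other assumed separate-site splits go down to 79%.
- *Separate sites, 4-month intake:* 88% to 91%.

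**The case against.** The strongest reply is that power may be ample. Study design and setting says that units offering home ripening also ripen in hospital, so survey sites may well hold both arms. A single whole-site design effect is then conservative, and the 64% and 71% overstate the loss. This stands. A reader might infer that the survey is underpowered, and the document does not support that: the shortfall appears under the plan's own method or with largely separate sites, and the site mix is not given.

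Secondly, no passage says that collection closes at 613. The stated 4 to 6 months would run well past it. This also stands, so the 64% describes the stated target and not a predicted outcome.

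Thirdly, a reader might infer that 276 evaluable home women are required. They are not, because plentiful hospital respondents compensate in part. If the design effect stayed at 3.25, a 15:85 split would match 276 per arm at a total of 276/(2 × 0.15 × 0.85) = 1,082, or about 162 home women.

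Fourthly, 43,200 births and 12 sites are minimums and extension is allowed. One more site of average size (3,600 births) gives 46,800 × 0.22 × 0.15 × 0.40 × 6/12 = 309 home returns in 6 months. So 6.5 months is a figure at the floor and not a forecast. However, reaching 307 home returns in 4 months would need about 60% more births (307/190 = 1.61), and the extension rule still names no home count.

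**Conclusion.** The point holds as an inconsistency in the stated sample size and duration. The 552 and 613 come from equal arms, while the plan expects about 15:85. On the minimum figures, 4 months yields 190 home returns against the 307 that an equal split implies, and 613 in total is reached in about 2 months with about 92 home women. At that target the plan's own method gives about 64% power instead of 90%. The full 4-month intake gives about 71% to 92%, depending on whether the design effect follows the larger clusters.

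The accrual result rests only on the article's figures. The power results also rest on ICC 0.05 and on the site mix. Power is 90% or more if the arms are mixed within sites and site is modelled, and about 79% to 82% at 552 evaluable in the separate-site splits tried. What is established is that the stated target does not support the 90% claim for the split the plan expects. It is not established that the survey will be underpowered.

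**What to change.** 1. Recompute and restate the survey sample size for the expected 15:85 split, giving the assumed mix of home and hospital women across sites and including site in the model.
2. State the resulting minimum number of evaluable home respondents, which need not be 276, and an expected duration that matches it.
3. Tie the existing extension rule and recruitment monitoring to that home-arm count as well as to recruitment by site.

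The cost is restated figures and possibly an online survey open a few weeks longer.
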